## Abstract

**Introduction:**

Infection promotes coagulation via a large number of molecular and cellular mechanisms, and this procoagulant activity has boosted basic and clinical research using anticoagulant molecules as therapeutic tools in sepsis. Heparin, which is a naturally occurring proteoglycan that acts by reducing thrombin generation and fibrin formation, has not been rigorously tested in a randomized clinical trial.

**Methods:**

Randomized, double-masked, placebo-controlled, single-center clinical trial. Patients are recruited through the emergency room at Hospital Universitario San Vicente de Paul. This is a 650-bed University Hospital in Medellín, Colombia and is a referral center for a region with approximately 3 million habitants. The recruitment process started on July 2005 and will finish on June 2007. Patients aged 18 years or older, males or females, hospitalized with clinically or microbiological confirmed sepsis, have been included. The interventions are unfractioned heparin in low dose continuous infusion (500 units per hour for 7 days) or placebo, additionally to the standard of care for sepsis patients in Colombia.

**Results:**

Our primary aims are to estimate the effects of heparin on hospital length of stay and change from baseline Multiple Organ Dysfunction (MOD) score. Secondary objectives are to estimate the effects of heparin on 28-day all-cause mortality, and to estimate the possible effect modification on 28-day all-cause mortality, in subgroups defined by source and site of infection, and baseline values of APACHE II score, MOD score and D-dimer.

**Conclusion:**

The available literature in animal and human research, and the understanding of the molecular biology regarding inflammation and coagulation, supports a randomized clinical trial for the use of heparin in sepsis. Our study will provide appropriate power to detect differences in valid surrogate outcomes, and it will explore important preliminary data for efficacy regarding the clinical end-point of mortality.

## Background

Sepsis is considered a leading cause of death worldwide with approximately 18 millions cases annually and a mortality rate of almost 30% [1]. In Colombia, the country in which this study will be conducted, there are no national estimates of sepsis incidence. However, our previous investigations have provided some relevant data: in a 650 bed University-based Hospital, bacteremia and/or sepsis were considered a main diagnosis in 7 out of 100 admissions to the emergency room; and blood cultures were requested in 2 out of 10 inpatients at some time during their hospitalization [2,3]. The overall 28-day sepsis mortality rate ranged from 25% to 40%, depending on the growth of microorganisms in blood cultures [2-4].

In the last two decades the accepted standard treatment for sepsis has resulted in only a slight decrease in mortality, and that decrease has been overshadowed by an almost 300% increase in incidence [5]. Unfortunately, the search for efficacious therapeutic approaches has largely failed and only a few of the recent interventions -as early goal directed therapy, activated protein C and low dose steroids- have shown success in improving survival [6,7]. However, these interventions were tested only in patients with severe sepsis and septic shock and although these groups exhibit the highest mortality, they may represent less than 50% of the total affected population [8,9]. Furthermore, these interventions necessitate special devices, tests or drugs that might be unavailable or simply unaffordable in resource-limited settings.

Several investigators have documented the close relationship between infection, inflammation and coagulation in sepsis [10-12]; and although clinically overt disseminated intravascular coagulation (DIC) may occur in only 30%–50% of septic patients, the activation of coagulation cascade is an early and common response to the infectious challenge [13-15]. In turn, most of the molecules involved in the pro-coagulant state that characterizes sepsis are also powerful generators or amplifiers of the inflammatory response [16,17]. The rationale behind anticoagulant treatments is that certain factors -activated protein C (APC), Antithrombin (AT) and Tissue Factor Pathway Inhibitor (TFPI) – are depleted, and the use of recombinant technology may replenish them. In contrast, heparin does not simply replenish what sepsis patients have depleted, it binds to and activates AT. As a consequence of this activation, heparin dramatically reduces thrombin generation and fibrin formation. Rather than artificially providing a component in the regulatory system, heparin takes advantage of the one existing molecule in its natural environment to increase its activity a thousand-fold [18].

Animal and human models have suggested that heparin, in addition to successfully inhibiting the coagulation cascade in sepsis, may also modulate a wide array of responses to infection [19-23]. Furthermore, the three clinical trials for recombinant anticoagulants allowed the use of prophylactic treatment for venous thrombosis with a dose of heparin of up to 10,000 or 15,000 units subcutaneously per day [24-26]. Although heparin was not given based on a random allocation, when those who did receive heparin were compared to those who did not in the placebo arms of the clinical trials, all three studies showed a higher mortality in the subgroups that did not receive heparin. Despite the obvious limitations of post-randomization comparisons, a constant result in three different study populations with variable entry criteria, along with the natural heterogeneity of the illness, strongly fosters the hypothesis that heparin might reduce, beyond its known anticoagulant and antithrombotic properties, the overall mortality for sepsis.

As noted in a recent editorial in JAMA [27], heparin is the most widely available, least expensive, and most frequently used anticoagulant; and despite the common recommendation of continuous infusion of low doses (300–500 units/hour) in the treatment of DIC [13,28], its potential and attractive usefulness as therapy for the treatment of sepsis has not been rigorously tested in a randomized clinical trial. Therefore, we are conducting a clinical trial for testing low dose continuous infusion of unfractioned heparin (500 units/hour for 7 days) as complementary treatment for septic patients.

Our primary aims are to estimate the effects of heparin on hospital length of stay and change from baseline Multiple Organ Dysfunction (MOD) score [29]. Secondary objectives are to estimate the effects of heparin on 28-day all-cause mortality, and to estimate the possible effect modification on 28-day all-cause mortality, in subgroups defined by source and site of infection, and baseline values of APACHE II score, MOD score and D-dimer.

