### Randomization and following procedures

The treatment assignment ratio is 1:1, fixed throughout the study. The allocation to heparin or placebo is defined by randomly permuted blocks of size 2, 4 and 6 generated by a random number generator (*ralloc *program, Stata co. 8.2, College Station, TX, USA). Complete treatments (four ampoules for each patient, marked with the same sequential number corresponding to the randomization scheme) are available in the emergency room's pharmacy center. The placebo is packed identically to the heparin sodium injection, and has the same color and volume as the heparin. Therefore, procedures for administration (i.e. loading dose and continuous infusion) are identical. Outcome measures are documented by medical research assistants masked to both the subject's intervention group assignment and the activated partial thromboplastin time (aPTT) values corresponding to specific days of the intervention period.

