### Sample size

Length of stay may be considered a time to event end-point, with patient discharge alive as the outcome. Those who die during the hospital stay will be considered as competing risks for this analysis because they are not censored observations. With a median length of stay of 11 days, a type I error of 0.05 and a type II error of 0.2, the estimated number of patients required to detect a relative hazard of being discharged alive of 1.3 is 231 [32]. This number of events may be achieved with a total sample size of 310 patients, assuming an overall hospital mortality of 25%.

MOD score data correspond to the case of longitudinal data with correlated measurements, and as such require special considerations for calculation of power and sample size [33]. The table 3 shows different estimates of power under different assumptions of correlation among repeated observations (ρ) and differences in rate of change (Δ) with a fixed sample size of 310 participants. This sample size also will have an 80% power to detect a 50% relative reduction in the secondary outcome of overall 28-day mortality.

**Table 3 T3:** Power estimates for differences (Δ) in MOD score with a fixed sample size of 155 patients per group and selected values of correlation (ρ)

ρ Δ	3 points	2 points	1 point
0.8	100%	99%	98%
0.5	100%	98%	97%

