### Interim monitoring

An independent Data and Safety Monitoring Board (DSMB) comprising three members with expertise in statistics, epidemiology and critical care practice are responsible for the interim monitoring process. The statistician in the data-coordinating center is the only person with access to the blind and the full data and he provides the required information, both overall for the interim quality assurance and specific by treatment group (efficacy and safety) exclusively for the DSMB.

The first interim was conducted when the first 103 study participants completed their 28-day vital status evaluation -approximately 9 months after study recruitment began. The second interim analysis will be conducted when 206 patients have been enrolled, approximately 16 months after the study initiation. Stopping guidelines for efficacy monitoring were determined according to the modified O'Brien-Fleming procedure [34,35]. With this procedure, the values for statistical significance will be 0.0006 and 0.0151 in the first (α_1_) and second (α_2_) interim analyses, respectively, for a final significance (α) of 0.0471.

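### Two unranked primary outcomes share one unsplit set of significance levels that names no outcome; if either may win, the familywise error is about 7% to 10%

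*Protocol article*

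**What the plan says.** The Background section (and the Results part of the Abstract) sets two primary aims side by side: "Our primary aims are to estimate the effects of heparin on hospital length of stay and change from baseline Multiple Organ Dysfunction (MOD) score". Neither is ranked above the other. The Analysis plan section tests them separately, with a log-rank test for length of stay and a random-effects longitudinal model for the MOD score.

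The Sample size section designs length of stay with "a type I error of 0.05 and a type II error of 0.2". Power for the MOD score is then tabulated on the same 310 patients (Table 3: "in MOD score with a fixed sample size of 155 patients per group and selected values of correlation"), and no significance level is given for that table.

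The Interim monitoring section says: "Stopping guidelines for efficacy monitoring were determined according to the modified O'Brien-Fleming procedure". It sets 0.0006 and 0.0151 for the two interim looks, "for a final significance (α) of 0.0471". No outcome is named. The first look followed completion of 28-day vital status in 103 patients and had already taken place. The second is planned at 206 enrolled patients.

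The article gives no division of alpha, no order of testing, and no statement of whether one primary or both must succeed.

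**The concern.** The article does not leave alpha to another document. It prints exact interim and final levels, which together make up one alpha budget of about 5%. A budget of that size fits one hypothesis, and the article has two primaries with separate tests. As written, nothing prevents both outcomes from being read against the same levels, with success claimed on whichever crosses.

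Two things are at stake. One is the false-positive rate of the trial's main claim. The other is the meaning of an early stop: a monitoring board holding these levels cannot tell from the text which outcome must cross them.

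**Working it through.** **Inputs.** Levels 0.0006, 0.0151 and 0.0471, and looks at 103 and 206 patients (Interim monitoring). Final look at 310 patients, alpha 0.05 and power 80% for length of stay (Sample size). Two assumptions are mine. Tests are two-sided, since the article does not state sidedness. Information is proportional to patients, giving fractions 103/310, 206/310 and 1. The correlation r between the two primary test statistics is not given, so it is varied. The ρ in Table 3 is the correlation among repeated MOD scores and does not supply r.

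**1. The article's own levels on one outcome.** The z thresholds are 3.432, 2.430 and 1.985. With correlation √(n_j/n_k) between looks j < k, the chance of crossing at any look under the null is 0.0524. The levels therefore amount to one budget of about 5%, slightly exceeded for a reason unrelated to multiplicity.

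**2. Two outcomes, either may win.** Without interim looks and at 0.05 each, independent tests give 1 − 0.95² = 9.75%. With the three stated looks and r = 0, the result is 1 − (1 − 0.0524)² = 10.2%. For correlated outcomes I simulated two three-look processes (2,000,000 trials):

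| r | At least one false rejection |
|---|---|
| 0 | 10.2% |
| 0.3 | 10.0% |
| 0.5 | 9.5% |
| 0.7 | 8.8% |
| 0.9 | 7.4% |

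**3. Two outcomes, both required.** The worst case is a real effect on one outcome and none on the other. The error is then at most the single-outcome rate, 5.2% at the stated levels.

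**4. A boundary for 0.025 per outcome.** The classical three-look O'Brien-Fleming constant for two-sided 0.025 is 2.272. Nominal levels are 2[1 − Φ(2.272·√(3/k))], which gives 0.00008, 0.0054 and 0.0231. Look 1 has already been taken at 0.0006. Keeping that level and using 0.0054 and 0.0231 afterwards spends 0.0253 per outcome. At r = 0 the chance of any false rejection is 1 − (1 − 0.0253)² = 5.0%, and it is lower for correlated outcomes (3.7% at r = 0.9 by simulation).

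**5. Power cost for length of stay.** Final look only, power ≈ Φ(drift − z).
- For a design with true 80% power at 0.05, the drift is 1.960 + 0.842 = 2.802. Power is Φ(2.802 − 1.985) = 79% at 0.0471 and Φ(2.802 − 2.272) = 70% at 0.0231.
- With 231 discharge events in total and relative hazard 1.3, the drift is √231 × ln(1.3)/2 = 1.994. Power is Φ(1.994 − 1.985) = 50% and Φ(1.994 − 2.272) = 39%.
- The two cases differ because 231 is the number needed per arm. Freedman's total is (1.960 + 0.842)² × (2.3/0.3)², about 462, and half of that is 231. The article uses it as the total, since 231/0.75 = 308 matches its 310. That is a separate issue and does not affect the error rates above.

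**The case against.** The strongest reply is that this is a condensed article, and that a success rule and the outcome attached to a stopping boundary often sit in the full protocol, the analysis plan or the monitoring board's charter. That would settle the matter if the article were silent on alpha. It is not: it prints exact final levels beside two unranked primaries, and the two do not fit as printed. If a rule exists elsewhere, citing it answers the point.

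Other parts of the reply stand and limit what can be said:

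- A reader might infer that the trial's false-positive rate simply is 10%. The article nowhere says that either primary alone counts as success, and it claims no 5% rate across the pair. The inflation is conditional on that rule.
- A reader might infer that each primary is explicitly assigned 0.05. That is stated only for length of stay. For the MOD score it is inferred from the single final level.
- Ten percent is the upper end. Length of stay and organ dysfunction in the same patients are plausibly correlated, perhaps strongly.
- A reader might infer from the timing of the first look that mortality is a third route to success. The Abstract, Background and Analysis plan all call mortality secondary, the Conclusion treats it as preliminary, and the interaction tests are labelled hypothesis-generating. Waiting for 28-day follow-up can be just a data cut-off.

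**Conclusion.** The point holds in conditional form. The article fixes one alpha budget, attaches it to no outcome, and names two unranked primaries with separate tests. If success on either counts, the familywise error is about 7% to 10% for r between 0.9 and 0, or roughly 1.4 to 2 times the 5.2% that the levels spend on one outcome. If both are required, it stays at about 5%. The article states neither rule.

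The figures assume two-sided tests, the MOD score judged at the same levels as length of stay, and information proportional to patients. The ambiguity about which outcome may stop the trial needs none of these assumptions. This should be settled before the second look; it does not invalidate the design.

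**What to change.** Before the second interim look, add one paragraph to the analysis plan and the monitoring board's charter that does two things.

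1. Name the outcome or outcomes to which the efficacy boundary applies.
2. State how error is controlled across the two primaries. One option is Holm within the group-sequential design: the smaller p-value is compared with the 0.025 boundary (about 0.0054 at look 2 and 0.0231 at the final look), and if it passes, the other is compared with the 0.05 boundary. A fixed order of testing, or requiring both primaries, would also do.

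The first look has been taken, so a new rule can govern only the second look and the final analysis. By the check above, leaving 0.0006 in place for look 1 makes almost no difference.

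No extra patients or data are needed to write the rule. The cost is power for a primary that is significant alone: for length of stay, about 79% falls to 70% in a design with true 80% power, or 50% to 39% with 231 events in total. Holding 80% power at 0.025 would take about 21% more events (559 against 462 by Freedman's formula). The stated power for length of stay should therefore be given at the level actually used. A fixed order spares the outcome tested first. Requiring both keeps the stated levels but lowers the chance of overall success.

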## Materials and methods

### Study design

Randomized, double-masked, placebo-controlled, single-center clinical trial.

### Population

An ideal therapy should be viable for septic patients at the earliest stage in their clinical course once the infectious process is suspected or confirmed, and not only at the point of admission to intensive care as has been the case for virtually all previous sepsis trials. Although the definitions for severe sepsis and septic shock have been relatively easy, the identification of that "less ill" population has been really hard to meet. In fact, currently we are lacking a standard definition for sepsis. We have shown [30] that in the setting of the proposed study, the classical systemic inflammatory response syndrome (SIRS) definition was not inclusive enough to identify the full spectrum of patients, since its sensitivity was less than 70% for a cohort with a median length of stay of 11 days and an overall hospital mortality of 21%. Thus, we are proposing a set of inclusion criteria that may be useful to include the wide spectrum of the syndrome. In addition to fulfilling the operational criteria for inclusion, we are restricting our population to the patients with a clinical picture as severe enough to require inpatient treatment.

Patients will be recruited, between July 2005 and June 2007, through the emergency room at Hospital Universitario San Vicente de Paul. This is a 650-bed University Hospital in Medellín, Colombia and is a referral center for a region with approximately 3 million habitants. Patients aged 18 years or older, males or females, hospitalized with a suspected or confirmed infection, unexplained fever, unexplained altered mental status or unexplained arterial hypotension (systolic blood pressure < 90 mm Hg or a decrease > 40 mm Hg) will be considered potentially eligible for the trial.

### Inclusion criteria (table 1)

**Table 1 T1:** Inclusion criteria – HETRASE study

**Modified CDC definitions for infection**	**General variables**	**Inflammatory variables**
1) Pneumonia	1) Temperature (oral or axillary) > 38°C or < 36°C	1) WBC > 12,000 μL^-1 ^or < 4,000 μL^-1 ^or with > 10% immature forms
2) Bloodstream infection	2) Heart rate > 90 beats/min	2) Plasma C-reactive protein > 5 mg/dL.
3) Clinical sepsis	3) Respiratory rate > 20 breaths/min	
4) Symptomatic urinary tract infection and other infections of urinary tract	4) Altered mental status determined by Glasgow Coma Scale < 15	
5) Intra-abdominal infections	5) Systolic blood pressure < 90 mm Hg or a decrease > 40 mm Hg	
6) Skin infections		
7) Soft tissue infections		
8) Superficial and deep surgical site infections		
9) Joint or bursa infections		

- Patients must have an infection defined by clinical and/or microbiological criteria in accordance with modified CDC definitions for nosocomial infections [31].

- Patients must present with one or more of the general variables *AND *one or more of the inflammatory variables, within 24 hours before admission to the study. These variables should not be attributable to an underlying disease other than infection or due to the effects of concomitant therapy.

### Exclusion criteria (table 2)

**Table 2 T2:** Exclusion criteria – HETRASE study

- Pregnant or breastfeeding.
- Platelet count < 60,000/mm^3^.
- Increased risk for bleeding: a) Any patient who has undergone major surgery, defined as surgery that required general or spinal anesthesia, performed within the 12-hour period immediately preceding admission to the hospital; any postoperative patient who demonstrates evidence of active bleeding; or any patient with planned or anticipated major surgery during the first 12 hours after admission to the hospital. b) History of: severe head trauma that required hospitalization, intracranial surgery, or stroke within 3 months of study entry; or any history of intracerebral arteriovenous malformation, cerebral aneurysm, or central nervous system mass lesion. c) History of congenital bleeding diatheses, such as hemophilia. d) Gastrointestinal bleeding within 6 weeks of study entry that required medical intervention unless definitive surgery has been performed. e) Trauma patients at increased risk of bleeding, for example: flail chest; significant contusion to lung, liver, or spleen; retroperitoneal bleed; pelvic fracture; or compartment syndrome.
- Patients with a known hypercoagulable condition including activated Protein C resistance; a hereditary deficiency of Protein C, Protein S, or antithrombin; presence of anticardiolipin antibody, antiphospholipid syndrome, lupus anticoagulant or homocysteinemia; or patients with a recently documented (within 3 months of study entry) or highly suspected deep venous thrombosis or pulmonary embolism.
- Patients taking or requiring the following medications: a) Therapeutic heparin, defined as UFH dosed to treat an active thrombotic or embolic event within the 12 hours prior to study entry or LMWH used at any dose higher or more frequent than the recommended dose on the product label for prophylaxis within the 12 hours prior to study entry. b) Warfarin, if used within 7 days of study entry. c) Thrombolytic treatment within 3 days of study entry (for example, streptokinase, rtPA, and urokinase). d) Glycoprotein IIb/IIIa antagonists within 7 days of study entry.
- Patients with known esophageal varices, chronic jaundice, cirrhosis, or chronic ascites.
- Presence of an advance directive to withhold life-sustaining treatment
- Patients not expected to survive 28 days given their preexisting, uncorrectable medical condition. This criterion includes patients with, or suspected to have, poorly controlled neoplasms or other end-stage processes, such as end-stage cardiac disease, prior cardiac arrest, end-stage lung disease, or end-stage liver disease.
- Patients with chronic renal failure on either hemodialysis or peritoneal dialysis.
- HIV positive patients with most recent CD4 count < 200/mm^3^.
- Patients who have undergone bone marrow, liver, lung, kidney or pancreas transplantation.
- Inability or unwillingness of patients or legal representative to give written informed consent.

- Pregnant or breastfeeding.

- Platelet count < 60,000/mm^3^.

- Increased risk for bleeding

- Patients with a known hypercoagulable conditions

- Patients taking or requiring anticoagulant medications

- Patients with known esophageal varices, chronic jaundice, cirrhosis, or chronic ascites.

- Presence of an advance directive to withhold life-sustaining treatment

- Patients not expected to survive 28 days given their preexisting, uncorrectable medical condition.

- Patients with chronic renal failure on either hemodialysis or peritoneal dialysis.

- HIV positive patients with most recent CD4 count < 200/mm^3^.

- Patients who have undergone bone marrow, liver, lung, kidney or pancreas transplantation.

- Inability or unwillingness of patients or legal representative to give written informed consent.

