### Methods for dealing with potential adverse events

General treatment for patients is left up to the medical team in charge of each patient, according to clinical practice guidelines for infectious diseases and critical care available at the institution.

Basic considerations for dealing with potential adverse events are:

- Infusion should be suspended indefinitely if there are *new *signs or symptoms of hemorrhage such as bleeding from gums, nosebleeds, extensive bruising, evidence of purplish skin areas or gastrointestinal bleeding.

- Infusion should be suspended indefinitely if there is an otherwise unexplained drop of 50% or greater in platelet count, or an absolute platelet count below 30,000 cells per mm^3 ^any time during the study.

- Infusion should be interrupted 2 hours before any percutaneous procedure or major surgery, and should only be resumed 1 hour after a percutaneous procedure or 12 hours after major surgery. In presence of bleeding complications with any of these procedures, infusion can only be resumed after normal results in coagulation tests, and no less than 24 hours after the procedure

- Infusion should be interrupted indefinitely if aPTT test is prolonged more than 60 seconds at any time during the infusion period.

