### Analysis plan

Overall study efficacy will be established using the intention-to-treat principle, in which patients are analyzed in the treatment group to which they are assigned at randomization. Length of stay may be considered a time to event time end-point with discharge as the outcome. The graphical presentation of these survival distributions for heparin and placebo groups will be estimated using the Kaplan-Meier method, and the test statistic for comparison between these two survival distributions will be based on the Log-rank test [32].

MOD score data correspond to the case of longitudinal data with correlated measurements, and as such require special statistical methods to account for the correlation among observations. To analyze this kind of clustered data, it is necessary to model both the regression of *Y *(the outcome measure) on *x *(the intervention) and the within-cluster dependence in a unified manner with the application of a random-effects model for longitudinal data [36].

For secondary outcomes, the comparisons will be presented as absolute and relative differences in 28-day mortality rates with exact 95% confidence intervals. The statistic to test this secondary null hypothesis will be the Chi-square test. Although the expectation is that randomization assists in balancing known and unknown prognostic factors, this assignment process is not a guarantee against the possibility that estimates of treatment effect will be modified by covariate imbalance. Accordingly, the estimated relative risk of mortality for heparin vs. placebo will be adjusted by the most important prognostic factors (age, APACHE II score and MOD score at baseline), using a multiple logistic regression model.

The natural heterogeneity of sepsis supports the importance of exploring the efficacy of the intervention among different subgroups of patients, as defined by characteristics of the illness. As hypothesis-generating analysis, the following interaction terms will be incorporated into the logistic model described before:

- Treatment * Source of infection (pneumonia vs. others)

- Treatment * Site of acquisition (community vs. hospital)

- Treatment * APACHE II score at baseline (continuous variable)

- Treatment * MOD score at baseline (continuous variable)

- Treatment * D-dimer at baseline (continuous variable)

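### The two 12-hour major-surgery exclusions are timed from hospital admission rather than study entry, so a non-bleeding patient can start heparin less than 12 hours after an operation

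*Protocol article*

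**What the plan says.** Item a of the bleeding-risk exclusions (Table 2, Exclusion criteria) has three clauses. The first excludes major surgery "performed within the 12-hour period immediately preceding admission to the hospital". The second excludes "any postoperative patient who demonstrates evidence of active bleeding", with no time limit. The third excludes patients with "planned or anticipated major surgery during the first 12 hours after admission to the hospital".

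The neighbouring timed exclusions use a different clock. Head trauma, intracranial surgery or stroke, gastrointestinal bleeding, venous thrombosis, therapeutic heparin, warfarin, thrombolytics and glycoprotein IIb/IIIa antagonists are all timed from study entry. The therapeutic-heparin exclusion is also a 12-hour window: "within the 12 hours prior to study entry".

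For patients already on study drug, the section on dealing with potential adverse events says "Infusion should be interrupted 2 hours before any percutaneous procedure or major surgery", and that the infusion "should only be resumed 1 hour after a percutaneous procedure or 12 hours after major surgery". The randomization section states that "procedures for administration (i.e. loading dose and continuous infusion) are identical" in both arms, so a first start includes a loading dose.

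**The concern.** The surgical exclusion exists to keep recently operated patients from starting an anticoagulant, so its clock should run to the moment study drug can start. It runs to hospital admission instead. The two moments are not the same. Patients are described as already hospitalized when considered, the inclusion criteria count their 24-hour window back from admission to the study, and a patient must have a defined infection, laboratory results and written consent before entry. No upper limit on the delay is stated.

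An operation in the interval between admission and entry therefore escapes the look-back clause altogether, and is caught by the look-forward clause only if it was planned or anticipated within the first 12 hours. The remaining safeguards are the active-bleeding exclusion and the stopping rules. These respond to bleeding, laboratory changes or later procedures. None of them delays a first dose because of the time since an operation.

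At stake is patient safety: a loading dose and infusion sooner after surgery than the article allows for resuming the same infusion.

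**Working it through.** The article gives no figure to reproduce, so this is a timeline check.

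**Set-up.** Hospital admission is hour 0, study entry is hour E and major surgery is hour S. The patient is not actively bleeding and meets no other exclusion. The rules and window lengths come from Table 2. E is not in the document and is assumed over a range.

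- Look-back clause: excludes −12 ≤ S < 0.
- Look-forward clause: excludes planned or anticipated surgery at 0 ≤ S ≤ 12.
- Less than 12 hours post-operative at entry: E − S < 12.

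**Unprotected hours.** This is how much of the 12 hours before entry could contain a completed operation that no timed clause excludes.

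- Reading A, the look-forward clause covers all surgery in the first 12 hours after admission: min(max(E − 12, 0), 12).
- Reading B, surgery in those first 12 hours was unanticipated and so is not covered: min(E, 12).

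**Needless exclusion.** This is how much of the 12-hour pre-admission window still excludes a patient whose operation is at least 12 hours old at entry (−12 ≤ S < 0 and E − S ≥ 12): min(E, 12).

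| E (h) | Reading A | Reading B | Needless exclusion |
|---|---|---|---|
| 0 | 0 | 0 | 0 |
| 3 | 0 | 3 | 3 |
| 6 | 0 | 6 | 6 |
| 12 | 0 | 12 | 12 |
| 18 | 6 | 12 | 12 |
| 24 | 12 | 12 | 12 |

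**Examples (assumed times).**

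- Surgery at hour 14, entry at hour 18: gap 18 − 14 = 4 hours. No timed exclusion is met on either reading.
- Unanticipated surgery at hour 2, entry at hour 6: gap 6 − 2 = 4 hours. Eligible under reading B.

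**Smallest gap the rules allow.** Once E exceeds 12 hours (reading A) or 0 hours (reading B), the smallest allowed interval from surgery to entry falls to about 0 hours. Surgery before admission is not the problem: if it passes the look-back clause, it is always more than 12 hours old at entry.

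**With study entry as the anchor.** The look-back clause excludes E − 12 ≤ S ≤ E. The smallest allowed gap is then more than 12 hours for every E, and all three columns of the table become 0.

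**Upcoming surgery.** The look-forward clause also misses an operation planned soon after a late entry but more than 12 hours after admission. This breaks no 12-hour rule, since the article asks only for a stop 2 hours before surgery.

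**The case against.** The strongest reply is that the two anchors nearly coincide in this trial. Recruitment is through the emergency room, study drug is kept in that unit's pharmacy, and the stated aim is early treatment. At E = 0 there is no gap on either reading. Under reading A there is none up to E = 12, and a patient taken to theatre within 12 hours of arrival will usually have had that operation planned at some point. Several conditions must hold together for a patient to slip through. These points stand as limits on frequency. They do not close the gap, because the article states no limit on the delay, and qualifying infections such as intra-abdominal and surgical-site infections make operated patients plausible.

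The 12-hour rule during treatment concerns resumption, so applying it to a first start is an inference and no stated rule is contradicted. That is correct. But the drug and the bleeding concern are the same, and a first start adds a loading dose. The dose is described as equivalent to prophylaxis, yet the 12-hour resumption rule was written for that same infusion.

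The planned subgroup by site of acquisition does not prove long delays. Infections acquired during the current stay would give a large E, but the article does not say whether that subgroup consists of such patients or of readmitted ones.

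A journal article may leave screening windows to the full protocol. Here, however, the criterion is printed with an explicit anchor, so the fault lies in what is stated.

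**Conclusion.** The concern holds. Both timed surgery clauses use a clock that does not run to the start of study drug, unlike the neighbouring timed exclusions. As printed, the rules admit a non-bleeding patient less than 12 hours after major surgery whenever the operation falls between admission and entry and outside the look-forward clause. That requires a delay of more than 12 hours if the clause is read to cover all early surgery, or any delay if the early surgery was unanticipated.

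The number of patients affected is not given and may be small. The hours tabulated rest on assumed values of E. Design, sample size and analysis are untouched. This is a safety defect in one eligibility rule, and it should be corrected because it bears on bleeding risk and is simple to repair.

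**What to change.** In both timed clauses of item a, replace hospital admission with study entry (or start of infusion) as the reference point. The post-operative clause then uses the wording already in the therapeutic-heparin exclusion, "within the 12 hours prior to study entry", and agrees with the 12-hour resumption rule. Leave the active-bleeding clause as it is.

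The cost is a wording amendment to one exclusion criterion. A few recently operated patients would be deferred until 12 hours after surgery or not enrolled, and a few now excluded without need would become eligible. The article describes recruitment as still under way, so the change could still protect patients yet to be enrolled.
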